### 11.3.4 Handling of missing, unused or spurious Data, including Drop-outs and Withdrawals

Missing data will be documented and, as far as possible, reasons for missingness will be evaluated. In case of substantial amounts of missing data >5%, imputation methods will be considered such as Hot Deck imputation.

### 11.3.5 Data Analysis

#### Efficacy analysis

Efficacy analyses are performed for the comparison of neutralizing titers against the wild type and escape variants at 30 days (primary endpoints of the study) and on breakthrough

infections of wild type/ escape variants (secondary endpoint) at 180 days. The main efficacy analysis is performed between the two randomized arms (Arm C: ChAdOx1-S prime & boost; Arm A: ChAdOx1-S prime and BNT162b2 boost).

Neutralising titer and breakthrough infection are both defined as binary quantitative variables.

Hypothesis testing between the two treatment arms will be performed using Chi testing and logistic regression including stratification variables.

Efficacy analyses will be performed on the ITT and PP populations. The analysis of the ITT population will be considered as the primary analysis. All statistical tests are two-sided with a significance level of 0.05.

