| Planned number of subjects        | N=2124 (n=124 have already been randomized into the homologous Vaxzevria arm, up to 1000 participants will be included in each of the other two arms)                                                                                                                                                                                                                                                                                                                                                                                                                                                                                                                                                                                                                                                                                                                                                                                                                                                                                                                                                                                                                                                                                                                                                                                                   |

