| Statistical methods & analyses | 
An interim analyses applying the Haybittle Peto rule for early stopping had been applied. Safety and efficacy have been analyzed on day 30 after n=200 patients had been randomized. level of neutralizing antibodies (primary endpoint) had been significantly lower in the homologous Vaxzevria arm compared to the heterologous (p-value < 0.001) this arm had been stopped. Already recruited participants in all arms will be further followed for durability of antibody response and the number of breakthrough infections. New participants in the two remaining arms are recruited with the aim to recruit up to 1000 participants in each of these two arms to analyse the number of breakthrough infections. Efficacy analysis will employ contingency table analysis,
                                                                                                                                                                                                                                                                   |

|  |                                                                                                          |
|--|----------------------------------------------------------------------------------------------------------|
|  | chi-square testing and a logistic regression adjusting for the stratifying variables study site and sex. |
|--|----------------------------------------------------------------------------------------------------------|

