### 1.3 Need of the Study

The immune escape variants are spreading worldwide. Local transmission of the B.1.351 is observed in several European regions while P1 cases are mostly still travel associated. In Austria, there is local transmission of the Czech variant B.1.258Δ in several regions, while the P1 variant from Brazil plays no role yet. However, B.1.351 local transmission is observed in Tyrol, where 20-30% of SARS-CoV-2 infections were caused by this immune escape variant in January/February 2021, but then controlled but not eliminated by intensive testing. In March and April the largest world-wide outbreak of B.1.1.7 + E484K, also an immune escape variant, was observed in Tyrol. Although, some of the diagnosed cases seemed to be false positive for the E484K mutation, still several hundred have currently already been confirmed, a number that is internationally still unprecedented. It is expected that until the winter infection season, that is likely to hit Europe after a phase of low-level infections in summer, the immune escape variants will make up a substantial portion of SARS-CoV-2 infections in the countries with high seroprevalence after the vaccine campaigns such as Austria. Therefore, the vaccine programs must build up an effective immunity against the wild-type virus as well as the immune escape variants.

ChAdOx1-S contributes considerably to the arsenal of vaccines purchased by the European Community. During this study we already recruited approximately 300 participants. So far, 100 for the homologous Vaxzevria group, 106 for the heterologous Comirnaty prime/Vaxzevria boost group and 13 for the homologous Comirnaty group reached day 30 and were analyzed for safety and efficacy. The data of this interim analysis has been evaluated by the Data Safety Monitoring Board, which recommended a discontinuation of the homologous Vaxzevria arm due to significantly inferior immune responses. However, the study needs to be continued to analyze durability of immune responses in the already recruited participants. Additionally, more participants will be recruited to be able to compare as already initially planned the number of breakthrough infections between the homologous Comirnaty and the heterologous group.

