## 4.1 Number of Patients

A total of 2124 subjects will be included in this study. Each arm of 1000 subjects will be vaccinated as it follows:

Group A: ChAdOx1-S prime and BNT162b2 boost

Group B: BNT162b2 boost prime and BNT162b2 boost

Group C: ChAdOx1-S prime and ChAdOx1-S boost (this arm has been closed after 124 subjects have been randomized to; therefore, the total number of subjects is reduced from 3000 to 2124).

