## 11. Statistics

### 11.1 Sample Size

The sample size is generated for the primary endpoint of a superiority testing of level of neutralizing antibodies against the B.1.351 variant between the two randomized study arms (arm 1: ChAdOx1-S prime & boost, arm 2: ChAdOx1-S prime and BNT162b2 boost). A comparison against arm 3 (BNT162b2 prime & boost) is exploratory and will be done descriptively.

In a study of Madhi  92% of participants showed neutralizing antibodies following vaccination with ChAdOx1-S prime & boost against the B.1.1.7 (British) variant and 58% against the B.1.351 (South African) variant. Focusing on the improvement of the heterologous vaccination with the Biontech boost against the South African variant with regard to primary the endpoint of neutralizing antibodies we consider a sample size of n=1000 per study arm as appropriate. With this sample size, we can detect an increase in the percentage of participants with neutralizing antibodies against the South African variant from 58% to 65.5% as statistically significant, with a power of >90% and alpha of 5%. If the increase is 10% the statistical power would be >99%.

For the secondary endpoint of efficacy against breakthrough infection with the B.1.351 variant, based on the current number of 8 new cases per week in Tyrol with the B.1.351 variant we expect 208 cases during the next 180 days with no change in rate of infection.

Currently, the B.1.351 is concentrated in 4 districts – Kufstein, Schwaz, Innsbruck Land and Innsbruck Stadt giving a total population of 416,758, this gives a rate of 49,9/100,000 people in 180 days. As not all cases are sequenced we estimate that only 5% of B.1.351 variants are detected, this would mean in total a rate of approximately 1000 cases per 100000 population of the B.1.351 variant would occur over 180 days – this means 10 cases per 1000. This scenario could lead to 10 cases in the ChAdOx1-S prime & boost arm (Arm 1) and 0 case in the ChAdOx1-S prime and BNT162b2 boost arm (Arm 2). In the extreme situation that all 10 cases occur in Arm 1, this would be statistically significant. However, due to the decreasing infection rates in Tyrol we would currently consider this an underpowered analysis and as such would perform a posthoc power analysis. In addition, a second immune escape variant, B.1.1.7.+E484K has recently occurred in Tyrol with over 900 cases until now. However, the development of this outbreak is currently not predictable.

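### Section 11.3.5 still makes heterologous versus the closed 124-person Vaxzevria arm the main breakthrough analysis, although recruitment continues to compare heterologous with Comirnaty

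*Protocol*

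**What the plan says.** In the protocol's labels, Group A is heterologous (arm 2 in section 11.1), Group B is homologous Comirnaty (arm 3) and Group C is homologous Vaxzevria (arm 1).

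- **Section 11.3.5, Efficacy analysis** covers titers at 30 days and "infections of wild type/ escape variants (secondary endpoint) at 180 days". With no distinction between the two endpoints it continues: "The main efficacy analysis is performed between the two randomized arms (Arm C: ChAdOx1-S prime & boost; Arm A: ChAdOx1-S prime and BNT162b2 boost". Testing is by chi-square and logistic regression, two-sided at 0.05.
- **Section 4.1** says of Group C that "this arm has been closed after 124 subjects have been randomized to". The synopsis gives the resulting total: "N=2124 (n=124 have already been randomized into the homologous Vaxzevria arm, up to 1000 participants will be included in each of the other two arms".
- **Section 1.3** gives the reason for further recruitment as a comparison of "the number of breakthrough infections between the homologous Comirnaty and the heterologous group", and describes this as part of the initial plan. The synopsis says the aim is to "recruit up to 1000 participants in each of these two arms to analyse the number of breakthrough infections", meaning Groups A and B.
- **Section 11.1**, in the text that sizes the primary antibody endpoint, says: "A comparison against arm 3 (BNT162b2 prime & boost) is exploratory and will be done descriptively". Its later breakthrough scenario is 10 cases in the Vaxzevria arm against none in the heterologous arm.

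**The concern.** Section 11.3.1 was revised to describe a two-arm, non-randomised trial after the Vaxzevria arm was discontinued. The main-analysis sentence in 11.3.5 reads as if that arm were still being filled. For the day-30 titer this does little harm, because A versus C is the randomised contrast and the interim result has already been obtained on it. For breakthrough infection it points to the wrong comparison.

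A versus C asks whether a Comirnaty boost protects better than a second Vaxzevria dose. A versus B asks how the mixed regimen compares with two Comirnaty doses. Only the second explains why up to 1000 people are enrolled in each of A and B. If 11.3.5 is followed, the main breakthrough result rests on 124 people in Group C. Up to 1000 people in Group B then have no role in the main analysis. Section 11 gives A versus B no hypothesis, margin, sample size or named test.

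**Working it through.** **The protocol's own figures (section 11.1).**
- Antibody power at 1000 per arm, two-sided 0.05: 58% v 65.5% gives 93.3% (stated as above 90%), and 58% v 68% gives 99.6% (stated as above 99%).
- Breakthrough rate: 8 × 26 = 208 cases; 208 / 416,758 = 49.9 per 100,000; 49.9 / 0.05 = 998 per 100,000, about 10 per 1000.
- 10/1000 v 0/1000: Fisher p = 0.0019, uncorrected chi-square p = 0.0015, so it is significant as stated.

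These figures reproduce. All of them describe C versus A with 1000 per arm, which can no longer be reached.

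**Group C at its actual size (n = 124, rate 1%).**
- Expected cases: 124 × 0.01 = 1.24, against 10 in the scenario.
- Chance of no case: 0.99^124 = 0.288.

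**Power in the protocol's extreme scenario (C 1%, A 0%), exact enumeration.**
- C 124 v A 1000, uncorrected chi-square: one case in C against none in A already gives p = 0.004. Power is therefore the chance of at least one case, 1 − 0.288 = 71%.
- C 124 v A 1000, Fisher: one case gives p = 0.11 and two give p = 0.012. Power is the chance of at least two cases, 1 − 0.288 − 124 × 0.01 × 0.99^123 = 35%.
- 1000 v 1000: 99% by chi-square, 93% by Fisher.
- 124 v about 124 (randomised participants only): 4% by chi-square, 0.2% by Fisher.

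The protocol specifies chi-square. It is unreliable with counts this small, as a single case deciding the result shows.

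**Precision with equal true rates r.** SE(log RR) = sqrt(1/(r·n1) + 1/(r·n2) − 1/n1 − 1/n2), and the interval is exp(±1.96·SE).

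| Contrast | SE at 1% | 95% CI at 1% | 95% CI at 3% (assumed) |
|---|---|---|---|
| A 1000 v C 124 | 0.947 | 0.16–6.4 | 0.35–2.9 |
| A ~124 v C 124 | 1.264 | 0.08–11.9 | 0.24–4.1 |
| A 1000 v B 1000 | 0.445 | 0.42–2.4 | 0.61–1.65 |

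The formula is a large-sample one, so the rows with 124 are rough. The 3% column is shown because the 1% rate is for B.1.351 only, whereas the endpoint counts wild type and escape variants.

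**What A versus B can deliver.** The 1% v 0% scenario was built for Vaxzevria against heterologous and does not carry over to two arms that both receive a Comirnaty boost. For an assumed 1% v 0.5% with 1000 each, power is 18% by Fisher and 24% by chi-square. By the normal approximation, 80% power would need about 4,673 per arm.

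**The case against.** **Breakthrough infection is secondary and its power is already conceded.** This is true: section 11.1 itself calls the analysis underpowered. That caveat concerns C versus A and blames falling infection rates, not the closure of Group C. It does not settle which comparison the continued recruitment serves.

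**The conflict can be overstated.** A reader might infer that the protocol names two rival deciding contrasts, that the synopsis tests A versus B, that 11.1 forbids such a test, and that both contrasts could be tested at 0.05 and the better one chosen. The documents do not support this:
- Only 11.3.5 names a main contrast. Section 1.3 and the synopsis state a purpose of recruitment.
- The synopsis sentence beginning "Efficacy analysis will employ contingency table analysis" names no arms. It adjusts for study site and sex, which are the randomisation strata of A and C.
- The sentence in 11.1 on the Comirnaty arm stands with the primary antibody endpoint. It is not expressly limited to that endpoint, but it does not address breakthrough infection.
- No passage tests both contrasts.

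**A versus B is non-randomised and unblinded, and A versus C is the only randomised comparison.** This stands. It shapes the remedy: A versus B has to be an adjusted estimate labelled as such, and the randomised comparison must be kept.

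**Details of a secondary analysis belong in the SAP.** Model details do. Here, though, the protocol states a rule, and the rule points away from the comparison the protocol says it is recruiting for.

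**Conclusion.** Wrong as written, for one endpoint. The main-analysis sentence in 11.3.5 keeps A versus C for breakthrough infection, after Group C closed at 124 and recruitment was redirected to A versus B. Following it leaves the stated reason for enrolling up to 1000 in each of A and B outside the main analysis. The comparison it does name expects 1.24 cases in Group C at the protocol's rate, and its interval for the risk ratio runs roughly from 0.16 to 6.4.

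This should be changed, but it does not undermine the trial. The primary antibody comparison is unaffected. A change of contrast improves relevance and precision without making the breakthrough analysis well powered.

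The figures assume full enrolment of A and B, no dropout, and the B.1.351 planning rate unless noted. About 124 participants randomised to A is implied by 1:1 allocation but not stated.

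**What to change.** **Section 11.3.5:** split the main-analysis sentence by endpoint.
1. Neutralizing titer at day 30: A versus C, in randomised participants only.
2. Breakthrough infection to day 180: A versus B, as the contrast for which recruitment continues. Report a risk or rate ratio with 95% CI, adjusted for site, sex and baseline factors already collected (for example age and calendar time of the boost), and label it non-randomised. Report A versus C in the randomised participants alongside, as a supportive low-precision estimate.

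**Section 11.1:** limit the exploratory and descriptive sentence to the antibody comparison with Comirnaty. State that the 10 v 0 scenario assumed 1000 in Group C and no longer applies.

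**Synopsis:** use the same wording, and name the arms to which chi-square and logistic regression apply.

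**Cost:** wording in three places and one adjusted model, with no new data or participants. A versus C can no longer be presented as the main breakthrough result. The change comes after the interim antibody results were seen, and the amendment should state this.

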If patient discontinues study participation for reasons unrelated to an adverse event, immunization of the patient will be continued according to the recommendations of the Austrian NIG (Nationales Impfgremium). No additional patient will be enrolled to replace that subject.

Reasons for removal investigational treatment or observation might include:

- Withdrawal of consent
- Administrative decision by the investigator
- Pregnancy
- Significant protocol deviation
- Subject noncompliance
- Serious Adverse event
- Other safety concern of the investigator or sponsor
- Death
- Lost to follow-up (participant repeatedly fails to return for scheduled visits without stating an intention to withdraw consent & he/she cannot be contacted by the study site after 3 contact attempts-these contact attempts must be documented in the participant`s medical record)

Participants that had been recruited during the first part of the study when this has still been conducted as a blinded and randomized study might request premature unblinding. In that case, participants might be kept part of the study after unblinding and will be further followed regarding durability of immune responses and breakthrough infections until day 180. If eligible, these participants might be included in a third vaccination.

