### 5.7 Visit VIII, X – XXXIII (every 7 days $\pm$ 2 day after boost shot)

Every 7 days ( $\pm$  2) after boost shot until Day 182 subjects have to undergo antigen or RT-PCR testing. If this test confirms an infection with SARS-CoV-2, the clinical course and outcome will be followed. Virus from swabs will be isolated and sequenced and further analyzed for immune escape.

In addition, subjects complete their reports in the eDiary or via telephone call.

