## 6.8 Blinding and Unblinding

All groups have already received the prime vaccination. The two groups that have received a prime with Vaxzevria (ChAdOx1-S) will be randomized into a group that receive again Vaxzevria (ChAdOx1-S) or Comirnaty (BNT162b2). The administration is blinded. The participants only are not informed in which arm they were randomized.

The syringes with the vaccines will be prepared in a separate room and brought into the vaccination room immediately before application. The unblinding will take place on day 90 post boost.

All participants recruited after closing of the homologous Vaxzevria arm that have received the prime immunization with Vaxzevria will receive the boost vaccination with Comirnaty in a non-blinded fashion.

All participants who have already received a prime with Comirnaty (BNT162b2) will receive Comirnaty (BNT162b2) again.

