#### Per-protocol population

The per-protocol (PP) population will include all patients who received the boost vaccination and fulfilled requirements up to day 30 after the boost. Major protocol deviations will be determined and documented prior to database lock.

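### Breakthrough infection is fixed as a yes/no outcome at 180 days with no allowance for time under weekly testing, so early end of observation understates the risk and can bias the arm comparison if stopping differs by arm

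*Protocol*

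**What the plan says.** Protocol Section 11.3.5 (Efficacy analysis) reads the secondary endpoint as "infections of wild type/ escape variants (secondary endpoint) at 180 days" and adds that "Neutralising titer and breakthrough infection are both defined as binary quantitative variables". The method follows: "Hypothesis testing between the two treatment arms will be performed using Chi 2 testing and logistic regression including stratification variables". The ITT analysis is primary, and "All statistical tests are two-sided with a significance level of 0.05". Section 11.3.2 defines the ITT set as all patients. The Synopsis (Statistical methods) repeats contingency tables, chi-square and logistic regression, directly after saying that the two remaining arms go on recruiting in order to analyse breakthrough infections.

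Detection is described elsewhere. Under Section 5.7, every seven days "after boost shot until Day 182 subjects have to undergo antigen or RT-PCR testing", and Section 5.10.2 starts this testing on Day 7. The only case definition, for vaccine failure in Section 7.2, requires two consecutive positive tests within a week.

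Several routes end observation of the two-dose regimen early:
- Full withdrawal of consent stops data collection (Section 4.4).
- Loss to follow-up is listed as a reason for removal (Section 4.4).
- Day-90 non-responders may receive a third dose between day 110 and day 180 (Section 5.11, third dose). Infections after a third dose are a separate secondary endpoint (Section 2.2).

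Section 11.3.4 says only that imputation, for example hot deck, will be considered if more than 5% of data are missing. No passage gives a censoring rule, a person-time measure or a rule for missed weekly tests.

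**The concern.** An infection found by repeated testing can enter the data only while testing goes on. A participant tested for 12 weeks and one tested for 26 weeks have different chances of showing an event, but in a two-by-two table or a logistic model each counts as one person with a yes or a no. Someone who stops early without a positive test must then be scored as uninfected, which treats unobserved weeks as infection-free, or set to missing, which discards the weeks that were observed.

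Absolute risk is affected in both arms. The comparison between arms is affected if time under test differs by arm. Sections 1.3 and 3.1 and the Synopsis continue recruitment specifically to compare breakthrough infections between the heterologous group (A) and the homologous Comirnaty group (B), without blinding and, for new participants, without randomisation. Nothing in that design makes time under test equal.

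**Working it through.** **Inputs from the protocol.** Section 11.1: 8 cases per week, population 416,758, 5% of variant cases detected, planning risk 10 per 1000 over 180 days, 1000 per arm. Sections 5.7 and 5.10.2: weekly tests from Day 7 to Day 182, which is 182/7 = 26 tests.

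**Inputs assumed.** The protocol gives no drop-out rate. I take a share d stopping early between 5% and 30%, stopping times uniform over follow-up, and a constant hazard.

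**1. The plan's own figures reproduce.**
- 8 × 26 = 208 cases.
- 208/416,758 = 49.9 per 100,000.
- 49.9/0.05 ≈ 998 per 100,000, about 10 per 1000.
- 10/1000 versus 0/1000: Fisher exact p = 0.0019; chi-square p = 0.0015 (0.0043 with continuity correction).

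**2. Risk when untested time stays in the denominator.** With hazard λ = −ln(1−r)/182, the observed risk is (1−d)·r + d·mean[1−exp(−λt)], with t uniform on 0 to 182. For small r this is close to r·(1−d/2).

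| d | Observed per 1000 (true risk 10) | Relative to truth |
|---|---|---|
| 5% | 9.75 | 0.975 |
| 10% | 9.5 | 0.95 |
| 20% | 9.0 | 0.90 |
| 30% | 8.5 | 0.85 |

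The relative loss is almost the same at true risks of 2%, 5% and 10%. Person-time recovers the truth: at d = 10%, 9.5 events over 0.95 × 1000 full follow-up periods is 10 per 1000.

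**3. Comparison between arms, equal true hazards, unequal stopping.** The risk ratio is about (1−d₂/2)/(1−d₁/2).
- 5% versus 20%: 0.90/0.975 = 0.92.
- 5% versus 30%: 0.85/0.975 = 0.87.

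Simulated type I error of the two-sided 5% chi-square test, 1000 per arm, 200,000 runs:

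| True 180-day risk | 5% vs 20% | 5% vs 30% | 10% vs 10% |
|---|---|---|---|
| 1% (planned) | 0.053 | 0.059 | 0.050 |
| 5% | 0.067 | 0.101 | 0.049 |
| 10% | 0.087 | 0.158 | 0.049 |

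Equal stopping leaves type I error at its nominal level. Unequal stopping raises it slightly at the planned risk, and more if infections turn out to be more common.

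**4. Third dose inside the window.** If two-dose follow-up ends uniformly between day 110 and day 180 (mean 145), an affected participant loses 1 − 145/182 = 0.203 of the period. The risk then falls by about 0.203 × the share affected: about 1% if 5% of an arm is affected and about 4% if 19% is. Section 1.3 reports 2 + 3 + 14 = 19 of 100 in Group C without antibodies to at least one tested variant, but ties the early third dose to wild type. The 2 of 100 with no response to any tested variant would give 0.203 × 0.02 = 0.4%.

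**The case against.** The strongest reply is that the harm is small and partly assumed. The endpoint is secondary, Section 11.1 already calls the analysis underpowered, and coding of incomplete follow-up is often settled in an analysis plan. At the planned 1% risk, type I error barely moves unless stopping differs by 15 to 25 percentage points. All of that stands. It does not remove the point, because the protocol fixes the binary analysis, and an analysis plan that moved to person-time would depart from it.

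Four stronger readings are tempting, and the documents do not support them.

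- *That the protocol scores untested weeks as infection-free.* It does not say so. This follows by default from a yes/no outcome in all patients with no censoring rule. Section 11.3.4 is weak, but it leaves imputation open.
- *That weekly tests are the only source of cases.* Section 5.9 admits unscheduled visits for a positive RT-PCR, and Section 4.3 mentions an N-antibody test on day 180.
- *That unblinding will drive unequal leaving in the continuing comparison.* Section 6.8 says "The unblinding will take place on day 90 post boost", but this concerns the randomised arms A and C. New A participants are open-label from the boost, and B was never randomised. Group C closed at 124, about 124 × 0.01 = 1.2 expected events at the planning risk. Section 4.4 does note that participants "might request premature unblinding", but it adds that they may stay in the study and be followed for breakthrough infections to day 180.
- *That the per-protocol set is frozen at Day 30.* It requires participants who "fulfilled requirements up to day 30 after the boost", but major deviations are determined up to database lock, and ITT is primary in any case.

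It is also fair to say that a time-based model adjusted for site and sex does not remove other differences, such as calendar time, between non-randomised groups.

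**Conclusion.** The point holds in a limited form. The protocol fixes a yes/no analysis at 180 days for an outcome seen mainly through weekly testing, and nothing in it accounts for time under observation. The 180-day risk is understated by about half the share that stops early: 2.5% to 15% in relative terms for assumed shares of 5% to 30%, with uniform stopping and a constant hazard. The comparison between arms is biased only if stopping differs by arm. The protocol gives no evidence that it will, but an open, non-randomised A versus B comparison gives no protection against it. At the planned 1% risk the effect on type I error is small (0.053 to 0.059 in the unequal cases shown). It grows with the infection rate, to 0.158 at 10% risk with 5% versus 30% stopping. This is a worthwhile, cheap improvement to a secondary endpoint and does not invalidate the trial.

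**What to change.** In Section 11.3.5 and the Synopsis, define the breakthrough analysis in one of two ways:
- time to first confirmed infection, dated at the first of the two positive tests required in Section 7.2; or
- confirmed infections per tested person-week.

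Censor at the earliest of:
- the last negative test before withdrawal, loss to follow-up or stopping of testing;
- any third dose, in the study or outside it, since later infections belong to a separate endpoint;
- Day 182.

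Use a Cox model, or a Poisson model with log tested time as offset, adjusted for site and sex. Report the 180-day Kaplan-Meier risk by arm. The chi-square and logistic results can stay as supportive analyses.

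The cost is wording only: weekly testing is already required, and the packages named in Section 11.3.5 fit these models. The downside is the assumption that stopping testing is unrelated to infection risk. That is least secure for the early third dose, which is offered because antibodies are absent, although the interim data suggest that few participants would be affected.
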